### Publication

The investigators plan to publish the trial results in a medical journal and did not enter any agreements restricting publication. Consent form and dataset can be made available on specific request. The study protocol can be found in Additional file 1.

### Enrolment

Eighty subjects who meet all of the inclusion criteria and none of the exclusion criteria with signed patient informed consent will be enrolled. Consent will be obtained by the intervening physician on a dedicated form. The scheduled time for recruitment of all patients is 2 years and is based on recruitment times in multiple previous studies of the center. There will be two follow-up evaluations at 12 and 24 months. The whole study is scheduled to take 4 years. During their participation in the clinical investigation, the patients will be insured against adverse events as defined by legal requirements.

### Inclusion criteria

Patient-related:Subject (or their legal guardian) has read, understood and provided written informed consent, which has been reviewed and approved by the Institutional Review Board.At least 18 years of age.Male, infertile female, or female participants of child-bearing potential practicing an acceptable method of birth control with a negative pregnancy test within 7 days prior to study procedure.Projected life expectancy of greater than 2 years.The ability to comply with protocol follow-up requirements and required testing.

Clinical:Lifestyle-limiting claudication or critical limb ischemia (meeting angiographic entry criteria) affecting a lower extremity (Rutherford stages 2–5). Patients with Rutherford stage 2 are only eligible after unsuccessful conventional and/or medical therapy.Resting ankle-brachial index (ABI) ≤ 0.8 in the study limb.Inflow and/or outflow lesion (including the SFA orifice) - if present - has been treated successfully (treatment in same procedure permissible)

Angiographic and lesion requirements (assessed intraoperatively):TASC A-D lesions with stenoses and/or occlusions ≤ 32 cm (this allows max 2 × 17 cm stents with 1 cm overlap and 0.5 cm overstenting each end of lesion).Popliteal artery is patent 5 cm proximal to the radiographic knee joint line.Reference diameter of 4.0–7.0 mm in proximal and distal treatment segments within the SFA.Patent SFA orifice (the proximal 5 mm after femoral bifurcation).At least one patent (<50% stenotic) inflow vessel present, proven angiographically. Study eligibility is given when inflow lesion has been treated successfully (inflow treatment in same procedure permissible). Successful treatment of inflow lesion is defined as < 50% stenosis without death or severe vascular complication.At least one patent (< 50% stenotic) tibial artery runoff to the ankle present, proven angiographically. Study eligibility is given when runoff vessel lesion has been treated successfully (outflow treatment in same procedure permissible). Successful treatment of outflow lesion is defined as < 50% stenosis without death or severe vascular complication.Guidewire has successfully traversed lesion and is within the true lumen of the distal vessel.

### Exclusion criteria

Pregnant or breast-feeding women.Lesion length > 32 cm.Flow-limiting occlusive disease of inflow or outflow arteries that cannot be treated sufficiently.Previous stenting or femoral bypass surgery in the target vessel.Clinical relevant aneurysmal disease of the abdominal aorta, ipsilateral iliac arteries, femoral arteries, or arteries of the knee.Rutherford stage 0, 1, or 6Non-atherosclerotic disease resulting in occlusion (e.g., embolism, Buerger’s disease, vasculitis).Septicemia.Ischemic stroke within the last 3 months.Any previously known coagulation disorder, including hypercoagulability.Morbid obesity or operative scarring that precludes percutaneous approach (at the physician’s discretion).Contraindication to anticoagulation or antiplatelet therapy.Known allergy to medication or contrast media used in this trial, if pre-treatment is not possible (according to the physician’s discretion).Known allergies to stent components, particularly nitinol.Severe calcification of the target lesion that impedes successful pre-dilatation.Current participation in another clinical research trial that has not reached its primary endpoint.The patient is institutionalized based on a legal verdict.

### Pre-interventional evaluation

Qualifying candidates will undergo the following evaluations:Medical historySubjective claudication status, walking impairment questionnaireCollection of previously available non-invasive studies (CDI ultrasound, CT, MR)Blood parameters: platelet count, APTT, PT, creatinine, fibrinogen, hemoglobin, hematocrit, leukocytes, and blood groupPregnancy test if indicated.

### Procedure

Vascular access is performed at the investigators discretion under local anesthesia, sedation, or general anesthesia. A contralateral or ipsilateral approach is permissible. A bolus of 5000 units of heparin is administered i.v. Diagnostic angiography is performed from the groin to the ankle (from the aortic bifurcation if no non-invasive imaging is available to document the patency of the inflow). Endovascular treatment of stenosed inflow (including the SFA orifice) and (after successful index lesion transversal) outflow lesions is permissible.

After successful lesion transversal and confirmation of inflow and outflow patency, the patient will be randomized one-to-one by a clinical research assistant (CRA). For this purpose, an online randomization program (www.sealedenvelope.com) will be used to generate a random 1:1 group allocation (block randomization). Only one limb is eligible for inclusion in the study.

A radiopaque calibrated ruler will be present on all radiographic images. Diameter measurements of the proximal and distal landing zone in a un-diseased SFA segment will be performed. These measurements will be used to select the balloon size for pre- and post-dilatation as well as the stent size according to the manufacturers’ stent-sizing table. After pre-dilatation with a subdiameter PTA balloon for 1 minute, the stent will be deployed and the post-dilated. The diameters for the pre- and post-dilatation balloon and the stent diameter will be determined after measuring the diameter of the non-diseased SFA at the proximal end of the intended treatment site. Table 1 gives the respective diameters of the stents for different SFA diameter ranges.

Stents will be deployed beginning with the most distal site. Spot-stenting of multiple lesions is permissible. Any balloon pre-dilated lesion should be covered by the device. Incomplete covered areas, if present, will be evaluated separately.

Stents will be assessed for correct implantation length by observing the relative proximal and distal stent markers with the corresponding delivery system markers. Deviations will be recorded as millimeter elongation or compression.

Completion angiography will be performed from the groin to the ankle (aortic bifurcation to ankle if inflow lesion treatment has been performed). After confirmation of absence of relevant residual stenosis the wire will be removed and radiography of the stent will be performed in two planes differing by ≥ 30 degrees.

Approved closure devices may be utilized at the physician’s discretion. Clopidogrel 75 mg orally once a day will be given for a minimum for 3 months post-procedure. A loading dose of 300 mg will be given immediately after the procedure in patients who did not receive clopidogrel before. Aspirin 100 mg orally once a day will be administered through the study follow-up. In patients with oral anticoagulation aspirin will be the only antiplatelet drug required.

The diameter of implanted stents will be measured at every 2 mm along the stent axis on DICOM images of the respective completion angiography using image processing software (Image J, NIH, MD, USA). To compensate for distortion errors a calibration must be present on each image. By comparing the measured diameter with the nominal diameter of the stent the relative amount of oversizing will be calculated as:$$ \%\kern0.5em Oversizing\kern0.5em =\kern0.5em \frac{D_n-d}{D_n}\times 100 $$

(Dn = nominal stent diameter, d = actual stent diameter after implantation and post-dilatation)

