### Stent types

The low COF group receives a thin-strut stent (Pulsar, Biotronik AG, Bülach, Switzerland) with minimal oversizing (according to manufacturer’s instructions), the high COF group receives a stiffer stent (Lifestent Flexstar, Bard Peripheral Vascular Inc., Tempe, AZ, USA) with maximal oversizing (according to manufacturer’s instructions). The stent sizing is based on group allocation and SFA diameter measurements according to a sizing table (Table 1, showing the device sizing according to the vessel diameter). The Pulsar-18 is a laser-cut self-expanding nitinol stent loaded on a low-profile 4 F compatible over-the-wire coaxial delivery system. The stent has a flexible, thin-strut, open-cell design with helically aligned peak-to-valley crowns and six radiopaque markers at each end. It is completely covered with an amorphous silicon carbide coating.

**Table 1 Tab1:** Stent diameter used according to the vessel diameter

		Nominal stent diameter (mm)		
Vessel diameter (mm)	Pre-dilatation	LifeStent	Pulsar-18	Post-dilatation
4–4.5	3	6	4	4
4.6–5.5	4	6	5	5
5.6–6.5	5	7	6	6
6.6–7.0	6	8	7	7

The LifeStent Vascular Stent System is comprised of the LifeStent Vascular Stent (stents 20–80 mm) and the LifeStent XL Vascular Stent (stents 100–170 mm). The devices contain self-expanding, flexible, nitinol stents that expand to a preset diameter upon exposure to body temperature. The stents are equivalent to one another in design with only one difference located at the crown section; the LifeStent contain six tantalum radiopaque markers on both the distal and proximal ends of the stent, while the LifeStent XL stent does not have markers. Figure 4 shows the two stent types in detail.

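### Randomisation comes before pre-dilatation, although failed pre-dilatation is an exclusion, and nothing requires the stent-selecting diameter to be recorded before the arm is known

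*Protocol article*

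**What the plan says.** All references are to the protocol article.

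- **Randomisation trigger (Procedure).** "After successful lesion transversal and confirmation of inflow and outflow patency, the patient will be randomized one-to-one". Neither vessel diameter nor pre-dilatation is part of the trigger.
- **Pre-dilatation (Exclusion criteria; Procedure).** One exclusion is "Severe calcification of the target lesion that impedes successful pre-dilatation". The step itself appears after the randomisation paragraph: "After pre-dilatation with a subdiameter PTA balloon for 1 minute, the stent will be deployed".
- **Diameter (Inclusion criteria; Procedure).** Eligibility needs "Reference diameter of 4.0–7.0 mm in proximal and distal treatment segments within the SFA", under a list introduced as "Angiographic and lesion requirements (assessed intraoperatively". The measurement is described after randomisation: "Diameter measurements of the proximal and distal landing zone in a un-diseased SFA segment will be performed".
- **Sizing (Stent types; Procedure).** "The stent sizing is based on group allocation and SFA diameter measurements according to a sizing table", which is Table 1. Procedure then gives a second basis for the diameter: the balloon and stent sizes "will be determined after measuring the diameter of the non-diseased SFA at the proximal end of the intended treatment site".
- **Blinding and analysis.** The CTA section blinds the two image readers; nothing is said about the operator or whoever reads the diameters. Statistical analysis makes intention-to-treat primary and adds a per-protocol analysis if deviations occur.

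**The concern.** Eligibility should be closed before the arm is revealed. Here one exclusion depends on the result of a step placed after allocation, so a judgement that calcification prevented pre-dilatation can be made by someone who knows which stent would follow.

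The diameter raises a related problem. It decides eligibility and also selects the Table 1 row, hence the stent size and the oversizing. The Background names oversizing as one of the two determinants of chronic outward force (COF), the factor under study. If the diameter is read with the arm known, a reading near a row boundary can move that factor.

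The endpoint makes this harder to repair afterwards. In-stent neointima does not exist for a patient who receives no stent, so declaring intention-to-treat does not supply a value for that patient.

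**Working it through.** **1. Order of steps**

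| Criterion | Could it be settled before allocation? | Does the text require that? |
|---|---|---|
| Lesion crossed; inflow and outflow patent | Yes | Yes, this is the trigger |
| Reference diameter 4.0–7.0 mm | Yes, on the diagnostic angiogram | No; measurement is described after the trigger |
| Calcification impeding pre-dilatation | Not as worded: it turns on the result of pre-dilatation | No; pre-dilatation is described after the trigger |

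**2. Does any step before stent choice need the arm?** In Table 1 the pre-dilatation balloons for the four rows are 3, 4, 5 and 6 mm, in one column common to both arms. So diameter reading and pre-dilatation can both be finished without the allocation.

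**3. What a row boundary does.** Across the four rows Pulsar-18 goes 4, 5, 6, 7 mm (a 1 mm change at 3 of 3 boundaries) and LifeStent 6, 6, 7, 8 mm (a 1 mm change at 2 of 3). As an illustration, I put the reference vessel diameter in place of the achieved stent diameter in the protocol's oversizing formula, (Dn − d)/Dn × 100:

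| Reading (mm) | LifeStent | Pulsar-18 |
|---|---|---|
| 5.5 | (6 − 5.5)/6 = 8.3% | (5 − 5.5)/5 = −10.0% |
| 5.6 | (7 − 5.6)/7 = 20.0% | (6 − 5.6)/6 = 6.7% |

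A 0.1 mm difference in reading at this boundary moves nominal oversizing by 11.7 points for LifeStent and 16.7 for Pulsar-18.

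**4. The protocol's sample size.** Inputs from Statistical analysis: difference 0.8 SD, two-sided 0.05, power 90%. The noncentral t calculation gives 33.8, so 34 per arm, with power 90.2%. Inflation: 34/0.85 = 40. The stated figures reproduce. Since 40 × 0.85 = 34 exactly, the 6 spare patients per arm are all taken up by the 15% dropout.

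**5. Loss of patients (assumed rates; the documents give none).** Remaining per arm = 40 × (1 − e) × 0.85, rounded down; needed per arm = 34/0.85/(1 − e), rounded up.

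| Extra loss e, both arms | Remaining per arm | Power (t test) | Randomised per arm to keep 34 |
|---|---|---|---|
| 0 | 34 | 90.2% | 40 |
| 5% | 32 | 88.3% | 43 |
| 10% | 30 | 86.1% | 45 |
| 15% | 28 | 83.6% | 48 |

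**6. Bias (assumed).** Suppose a share e is removed from one arm only, and those removed would have differed by δ from that whole arm's mean. The mean of those kept then shifts by δ × e/(1 − e). With δ = 1 SD and e = 5%, 10% and 15%, the shift is 0.05/0.95 = 0.05, 0.10/0.90 = 0.11 and 0.15/0.85 = 0.18 SD, against a design difference of 0.8 SD.

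**The case against.** A reader might infer that every patient is randomised before the vessel is measured. The text does not establish this. Enrolment admits only subjects who meet all criteria; the lesion requirements are assessed during the procedure; diagnostic angiography comes before randomisation; and a calibrated ruler is on all images. Nor is the sizing paragraph strictly chronological: it describes deployment before saying how the sizes are determined. An early diameter check may well be made. What stands is that the trigger does not demand it and nothing requires the Table 1 row to be recorded first.

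A reader might also infer that patients are in fact removed with the arm known, and that the randomised comparison is thereby broken. No section prescribes removal, and intention-to-treat is primary. Because the balloon is the same in both arms, physical failure of pre-dilatation does not depend on allocation. Any bias must come from judgement about what counts as impeding, for which neither rate nor direction is shown.

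On sizing, different stent sizes by arm are the intervention, and the text does not say who reads the diameter. Achieved oversizing is measured every 2 mm after implantation, and a regression of neointima on COF is planned regardless of arm. A shifted size would thus be recorded in the exposure data, though the primary between-arm t test would still carry it.

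Finally, the flow diagram (Fig. 3), the schedule (Fig. 5) and the full protocol (Additional file 1), none of which I have seen, might state the timing more finely. That tempers the diameter point. It does less for pre-dilatation, where the article itself states both the trigger and the criterion.

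**Conclusion.** The point holds with limits. It is firmest for pre-dilatation: as written, one exclusion criterion can be settled only after allocation. For the diameter, the weakness is that the text permits an arm-aware reading, not that it prescribes one. Discretion is widened because Procedure bases the diameter on both landing zones in one place and on the proximal end in another, and cites both a manufacturers' sizing table and Table 1. Those statements must be reconciled.

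The size is unknown because no rate is given. Under the assumed extra loss of 5% to 15% per arm, power stays between 88.3% and 83.6%; under one-sided removal with a 1 SD difference, the shift is 0.05 to 0.18 SD. Neither figure is evidence that bias has occurred. The severity is moderate: worth correcting because prevention is cheap and a lost endpoint value cannot be recovered in analysis, but not a reason to regard the comparison as invalid.

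**What to change.** **Patients still to be enrolled.** Amend Procedure so that the reference diameters and Table 1 row are recorded and pre-dilatation is completed before the allocation is released. Nothing up to that point depends on the arm.

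**Patients already randomised.** Report by arm every patient who failed the diameter or pre-dilatation criterion after allocation, or who received no stent. State that the primary endpoint is undefined for those without a stent, and show a sensitivity analysis over a stated range of values for them. Keeping them in the intention-to-treat set without saying what outcome they carry would not be enough.

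**Cost.** One paragraph of amendment, an online randomisation call made a few minutes later, and one extra table and sensitivity analysis. The sample size stays at 34 evaluable and 40 randomised per arm. The real downside is timing: recruitment began in October 2015 and was due to end in October 2017 (Abstract) or December 2017 (Trial status). An amendment during recruitment leaves two randomisation points in one trial, so the report should say how many patients were randomised under each.

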### Follow-up

At 12 and 24 months, patient receives contrast-enhanced CT angiography, clinical assessment, blood tests, ABI, and BIQ.

### CTA

Patients will be scheduled for two CTA control examinations, after 12 and after 24 months. Stent diameter and true lumen diameter will be measured on DICOM images every 2 mm along the stent axis to quantify the relative amount of in-stent restenosis as:$$ \%\kern0.5em Restenosis\kern0.5em =\kern0.5em \frac{D_s-{d}_l}{D_s}\times 100 $$

(D_s_ = stent diameter, D_l_ = lumen diameter)

For patients who receive target lesion revascularization or bypass surgery, the pre-operative CTA or angiography will be used to determine the amount of in-stent neointima at the time of the re-intervention.

All metallic stents generate some kind of blooming artifacts at CT imaging with a big variation between the different available stents. To face this issue, several techniques for CT imaging and reconstruction have been proposed, and most of them will be combined in the present study. In this trial, CT angiographies will be obtained with a third-generation Dual Source scanner, and the highest possible spatial resolution will be obtained, since blooming artifacts decrease with increased spatial resolution. Slice collimation will be 2 × 64 × 0.6 mm, and matrix size will be 512 × 512 pixels. Furthermore, image raw data will be reconstructed under application of an iterative reconstruction technique (Advanced Modeled Iterative Reconstruction - ADMIRE) and using a dedicated edge-enhancing kernel. Finally, the three-dimensional reconstruction of multipath-centered curved planar reformations (mCPR) will further facilitate the almost artifact-free assessment of the in-stent lumen.

All measurements will be undertaken on dedicated PACS stations (IMPACS EE R20 XVI SU1, AGFA Healthcare, Mortsel, Belgium) by two independent investigators with a minimum experience of 4 years with the software, blinded to patient and clinical information and group allocation.

Figure 5 shows the schedule of enrolment, all interventions and assessments.

**Fig. 5 Fig5:**
[figure not shown]
Schedule of enrolment, interventions, and assessments

### Statistical analysis

Sample size calculation is based on the primary endpoint at 1 and 2 years represented by the percentage of in-stent neointima formation (relative to the stent diameter). Statistical significance between the groups will be tested using a *t* test at a level of significance of 0.05. To detect a difference of 0.8 standard deviations with a statistical power of 90%, a sample size of 34 patients in each group is required. With a maximum dropout rate of 15%, 40 patients will be randomized per group.

A two-sided *t* test will be used to compare amount of neointima between the two treatment groups. In case of non-normally distributed data, appropriate normalizing transformations will be applied. To evaluate the degree of association between the extent of chronic outward force (by using the data presented in Fig. 4 showing COF of stent fabricates according to stent diameter) and the amount of in-stent neointima, a linear regression analysis will be performed independently of the stent allocation group. Primarily, analysis will be based on intention-to-treat. If protocol deviations occur, the analysis will be performed both on an intention-to-treat and on a per protocol basis.

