### Secondary objectives

Secondary objectives are the amount of in-stent neointima at 2 years, device- and procedure-related adverse events according to ISO 14155:2011 and target lesion revascularization (TLR) rate. In patients undergoing TLR the amount of in-stent neointima will be assessed by calibrated quantitative angiography at the time of the secondary intervention since no CT angiography will be available for these patients.

Technical success defined as successful stent deployment and absence of significant residual stenosis as well as patent in- and outflow at completion angiography.

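### The 24-month neointima comparison rests on a t test that ignores the same patients' 12-month reading; a two-visit mixed model guards better against selective loss, with a small gain in precision

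*Protocol article*

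**What the plan says.** The Statistical analysis section names one method for comparing the arms, a two-sided t test: "test will be used to compare amount of neointima between the two treatment groups". A normalizing transformation is allowed, and intention-to-treat is the primary basis. The linear regression on chronic outward force is a separate question and sets the allocation aside. The same section bases the sample size on neointima at both 1 and 2 years, so the t test is the stated method for the 24-month comparison too. No model joins the two visits.

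The 2-year reading is secondary: "Secondary objectives are the amount of in-stent neointima at 2 years". Both readings are scheduled in every patient: "At 12 and 24 months, patient receives contrast-enhanced CT angiography". Loss is expected: "With a maximum dropout rate of 15%, 40 patients will be randomized per group".

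One rule bears directly on the point. Under Secondary objectives and under CTA, patients who have target lesion revascularization or bypass surgery receive a neointima value from imaging at the re-intervention. The article does not say which visit's comparison that value enters, does not define the 24-month analysis set, and gives no rule for a CTA that is simply missed.

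**The concern.** A two-sample t test at 24 months needs a 24-month value. Without imputation, it treats the patients who have one as a random sample of their arm. The design supplies evidence on whether that is so: the same quantity was measured a year earlier in the same patients. That earlier value is likely to be correlated with the later one and may be related to who fails to return. The t test uses neither fact.

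If the chance of missing the second CTA depends on 12-month neointima and the arms differ, the two arms lose different parts of their distributions and the observed difference shifts. Neointima at 2 years is part of the stated trial objective, so the estimate matters even though the endpoint is secondary. The 12-month primary comparison is not touched.

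**Working it through.** **The plan's own figure.** Inputs, all from Statistical analysis: "test at a level of significance of 0.05"; two-sided; "To detect a difference of 0.8 standard deviations with a statistical power of 90" per cent; "a sample size of 34 patients in each group is required". With noncentrality 0.8 × √(n/2) and 2n − 2 degrees of freedom, the noncentral t gives power 0.893 at n = 33 and 0.9015 at n = 34. Then 34 / (1 − 0.15) = 40. Both figures reproduce.

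**Assumed inputs.** The article gives neither the correlation ρ between the 12- and 24-month readings nor the pattern of loss in year 2. Both are varied below. The main case takes 40 per arm read at 12 months and 34 at 24 months. This spends the whole stated 15% in year 2, so it is the most the plan's own allowance permits.

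**Precision, missingness at random.** In units of SD², the variance of an arm mean at 24 months is

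- t test: 1/34
- joint model of both visits: (1 − ρ²)/34 + ρ²/40

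For ρ = 0.7: 0.51/34 + 0.49/40 = 0.0150 + 0.01225 = 0.02725. The effective n is 1/0.02725 = 36.7, and the standard error ratio is √(0.02725 × 34) = 0.963.

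| ρ | effective n per arm | reduction in SE | power, normal approximation (t test 0.910) |
|---|---|---|---|
| 0.3 | 34.5 | 0.7% | 0.913 |
| 0.5 | 35.3 | 1.9% | 0.920 |
| 0.7 | 36.7 | 3.7% | 0.929 |
| 0.9 | 38.7 | 6.3% | 0.941 |

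If everyone read at 12 months is also read at 24 months, the two variances are equal and the gain is zero.

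**Bias, missingness dependent on the 12-month reading.** Simulation with bivariate normal readings, within-arm SD 1 and a true difference of 0.80 at both visits. The log-odds of missing the 24-month reading are linear in the 12-month reading (slope per SD over both arms), with 15% missing overall. The last column gives a value to the highest 10% of 12-month readings, as a stand-in for the re-intervention rule, and keeps 15% missing overall among the others.

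| ρ | slope | t test, no re-intervention values | t test, highest 10% keep a value |
|---|---|---|---|
| 0.6 | 1.0 | 0.760 | 0.832 |
| 0.6 | 1.5 | 0.732 | 0.830 |
| 0.8 | 1.0 | 0.748 | 0.845 |
| 0.8 | 1.5 | 0.712 | 0.842 |

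Taking the slope per within-arm SD instead moves each entry by less than 0.01 (lowest 0.704). In that version the joint estimate was also computed, and it was 0.80 in every scenario, with or without the kept values. With 7.5% missing, the t test gives 0.74 to 0.77 without re-intervention values and 0.81 to 0.82 with them. With no true difference and the same dropout mechanism in both arms, the t-test difference is 0 within simulation error.

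**Why the sign changes.** Without re-intervention values, the arm with more neointima loses more patients (20.5% against 9.5% at ρ = 0.8, slope 1.5), and they come from its top end. Once the top end is kept, the losses come from the upper middle of the pooled distribution. Those patients lie further above the mean of the low arm than of the high arm, so the low arm's mean falls more and the difference widens.

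**Scale.** The t-test standard error is √(2/34) = 0.243 SD. The bias of 0.04 to 0.09 SD in the first results column is 0.04/0.243 = 0.16 to 0.09/0.243 = 0.37 of it.

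**The case against.** The strongest reply is that the article condenses a fuller protocol. Handling of missed visits commonly sits there or in a statistical analysis plan, and a t test between randomized arms at one visit is a valid method. That stands as far as missing-data rules go: their absence here is not the point, and restriction to patients with a 24-month reading is an inference from how an unimputed t test works. It does not dispose of the method, which the article does state.

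The second reply is the re-intervention rule. A reader might infer that patients with heavy neointima vanish from the 24-month comparison and that the difference is therefore understated. The documents do not support that. Re-intervened patients, plausibly those with the most neointima, receive a value, and under that rule the simulated error is upward. The rule does not remove the problem. The Discussion itself describes revascularization in claudicants as dependent on subjective pain, urgency and resources, so some patients with high neointima will have no re-intervention and may still miss the CTA.

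Third, the effect is small and conditional. It needs an arm difference, or dropout that works differently by arm. It rests on an assumed correlation and slope, and it amounts to a fraction of one standard error. All of that stands, and it limits the weight of the point.

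**Conclusion.** The stated 24-month analysis is a weaker choice than one the planned data already allow. Under the assumptions above (ρ 0.6 to 0.8, slope 1 to 1.5, 15% missing in year 2), a true 0.80 SD is read as about 0.71 to 0.76 SD, or about 0.83 to 0.84 SD if the highest readings are retained through re-intervention imaging. The second range is illustrative: it assumes a sharp cut-off at the top 10% and a substituted value equal to the 24-month value. The direction of the error is therefore not fixed; what holds is that the joint estimate stays at 0.80 in both settings.

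Three stronger readings are not supported: that the t test is biased whatever the missingness, that it necessarily understates the effect, and that much power is lost. The gain in precision is 1 to 6% of the standard error and disappears with complete pairs. With no arm difference and a shared dropout mechanism there is no bias, so this route produces no false positive. The point concerns a secondary objective and is worth acting on mainly because the change is cheap.

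**What to change.** Keep the 12-month t test as the primary analysis. For 24 months:

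- Fit one linear mixed model to both visits with arm, visit, arm-by-visit and an unstructured 2 × 2 covariance, including every randomized patient with at least one reading.
- Model the 12-month value as an outcome, not as a covariate. It is measured after randomization, and adjusting for it would remove the part of the treatment effect already present at 12 months.
- State how readings taken at re-intervention enter: which visit they count for, and how values taken at unscheduled times or by angiography are handled. The t test needs the same rule.
- Report the 24-month arm contrast with its 95% confidence interval, and show the t test as a sensitivity analysis.

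The cost is analysis wording, with no new data or patients. The model relies on missingness being at random given the 12-month reading, which is weaker than the completely random loss that an unimputed t test generally needs but is still an assumption. It also adds one model to describe.
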